
### Descriptives

#### T0 measure (parents/main caretakers)

##### Socioeconomic status

Following recent studies in the Netherlands [94, 95], parental education level will be used as an indicator of socioeconomic status (SES), which has been regarded the most powerful indicator of SES [96–98]. To this end, the primary caregiver will report the education level of the mother and the father of each participant. Educational levels will be rated according to the Dutch Standard Education Classifications (Statistics Netherlands, 2021), which corresponds to the International Standard Classification of Education (ISCED; [99]). Following the ISCED classifications, parental education levels will be coded using an 8-point scale, with education levels including the following: 0 = *no education/early education*, 1 = *primary education*, 2 = *lower secondary education* (e.g., junior secondary school, middle school, junior high school), 3 = *upper secondary education* (e.g., senior secondary school, [senior] high school), 4 = *post-secondary non-tertiary education* (e.g., technician diploma, primary professional education), 5 = *short-cycle tertiary education* (e.g., [higher] technical education, higher/advanced vocational training, associate degree), 6 = *bachelor’s degree or equivalent*, and 7 = *master’s degree, equivalent or higher*. Parental education level will be based on the highest completed parental education level per household. That is, if a child has one parent with upper secondary education (i.e., 3) and another parent with a bachelor’s degree (i.e., 6), then we will code this child’s parental education with bachelor’s degree (i.e., 6).

##### Ethnicity

Ethnicity will be dichotomized as Dutch or non-Dutch based on where parents/main caretakers and their child is born.

*Intervention status* will be dummy-coded (0 = *control*, 1 = *HFPM program*).

## Study procedures

### Measures

#### Questionnaires T0, T1, T2, T3, T4, and 1-year follow-up T5

Girls, parents/main caretakers, teacher-mentors, and trainers will receive the online questionnaires hosted by Qualtrics at T0, T1, T2, T3, and T4 and at 1-year follow-up T5 via email by well-trained PhD students. After 1 week, participants will be receiving a reminder via email, followed by contact by telephone after another 3 days. Reminders will be sent by the teacher-mentors and PhD students will be responsible for the telephone calls. Table S1 describes the burden (in minutes) for girls in both groups, Table S2 for parents/main caretakers, and Table S3 for trainers.

#### Observations co-rumination T0 and T4

For a detailed description of the PTT, please see the section “Primary outcome variables.” The duration of the PTT is 30 min. The video recordings will be conducted by trained research assistants through Teams (students Developmental Psychopathology of the Vrije Universiteit Amsterdam) and will be supervised by both PhD students.

### Incentives

#### Screening

Girls who participate in the screening will receive a present worth 2.50 Euro.

#### T0 t/m T5 measures

Girls will receive a voucher of 10.00 Euro after completing each measurement.

#### Participation in the prevention program

To encourage dyadic app use during the period of November 2023 and April 2025, friendship dyads will build up a credit of 2.50 euros per week when they both complete daily monitoring (three times a day) and journaling (three times a day) for six out of the seven weekdays. Study personnel will email parents and girls weekly regarding the number of times girls used the app that week, and whether they will earn the weekly credit.

### Trial status

Protocol version 2, dd. 10–11-2023. Recruitment of schools started in December 2022, with recruitment of girls beginning in August 2023. Recruitment of girls will be finalized December 2025.

## Data analysis plan

Note that only the principal features of the statistical methods for primary and secondary outcomes are reported in this section. For an elaborate description of the analyses methods used to test the hypotheses, please see the Statistical Analyses Plan (SAP) in Supplementary Materials.

### Statistical methods for primary and secondary outcomes

Hypothesis 1 “Girls in the intervention group will have a greater reduction in co-rumination about distress and difficult emotions and feelings, (and thereby) internalizing symptoms and negative affect during the intervention period, immediately after the intervention period and after 1-year follow-up, relative to girls in the control condition” will be tested via (a) a multi-level parallel process, dual latent growth curve model (with co-rumination measured via self-report) and (b) a multi-level autoregressive cross-lagged model (with co-rumination measured via observation [100, 101]).

For analysis (a) with co-rumination measured via self-report (T0 to 1-year follow-up T5), we will use multi-level parallel process, dual latent growth curve (LGM) models, with intervention arm as the exogenous predictor variable, growth rate of co-rumination as the mediating variable, and growth rate of internalizing symptoms and negative affect as (correlated) outcome variables. See Fig. S3 for a simplified visual representation of this model.

For analysis (b) with co-rumination measured via observations (T0 and T4), we will use a multi-level autoregressive crossed-lagged model, with intervention arm as the exogenous predictor variable (relative change from T0 to T4 in) co-rumination as the mediating variable and (relative change from T0 to T4 in) internalizing symptoms and negative affect as (correlated) outcome variables. See Fig. S4 for a simplified visual representation of this model.

Hypothesis 2 “Girls in the intervention group will have (a) a later onset of depressive symptoms or a later onset of depressive disorder and (b) less dyadic depression contagion during the intervention period, immediately after the intervention period and after 1-year follow-up, relative to girls in the control condition” will be tested using discrete-time survival analysis [102] and via actor-partner interdependence modeling [103], respectively.

Specifically, discrete-time survival analysis (DTSA) will be used to investigate whether girls in the intervention group have a later onset of depression symptoms or disorder compared to girls in the control arm. Note that this hypothesis focuses on individual rather than dyadic outcomes. To adjust for individuals clustered within dyads, we will adjust the standard errors using a sandwich estimator [104]. Furthermore, a prospective change, Actor-Partner Interdependence Model (APIM) will be used to investigate whether dyads in the intervention condition will experience less dyadic depression contagion compared to dyads in the control arm from T0 to 1-year after follow-up. We will use multi-group comparisons to test whether contagion effects are less strong in the intervention arm compared to the control arm.

Hypothesis 3 “Girls in the intervention group will demonstrate (a) less anxiety problem talk and will have a (b) later onset of anxiety symptoms or a later onset of anxiety disorder and (c) less dyadic anxiety contagion during the intervention period, immediately after the intervention period, and after 1-year follow-up, relative to girls in the control condition” will be tested using multi-level LGM, DTSAs, and multi-group APIM, respectively.

Specifically, a multi-level LGM with intervention arm as the exogenous predictor variable and growth rate of anxiety problem talk as the outcome variable will be used to test whether girls in the intervention arm demonstrate less anxiety problem talk compared to girls in the control arm. Furthermore, DTSAs of anxiety symptom onset and anxiety disorder onset with intervention condition as an exogenous predictor will be used to test whether girls in the intervention group have a later onset of anxiety symptoms or disorder compared to girls in the control arm. Lastly, a multi-group (i.e., intervention versus control condition) APIM will be used to investigate whether dyads in the intervention condition will experience less anxiety contagion compared to dyads in the control arm from T0 to 1-year after follow-up.

Hypothesis 4 “Girls in the intervention group will experience better friendship quality, higher levels of positive affect and higher levels of interpersonal responses to positive affect of the dyad friend, during the intervention period, immediately after the intervention period and after 1-year follow-up, relative to girls in the control condition” will be tested using multi-level LGMs for each outcome, respectively. Specifically, three multi-level LGMs with intervention arm as the exogenous predictor variable and growth rate of friendship quality, positive affect, and interpersonal responses to positive affect as the (potentially correlated) outcome variables, will be used to test whether girls in the intervention arm experience more improvements in friendship quality, a faster growth in positive affect and faster growth levels of interpersonal responses to positive affect, compared to girls in the control arm.

Hypothesis 5 “The hypothesized intervention effects on co-rumination will be mediated by the development of mindfulness skills, emotion regulation skills, and problem-solving skills during the intervention period, immediately after the intervention period and after 1-year follow-up” will be tested using (a) a multi-level parallel process LGMs (for self-reported co-rumination) and (b) a multi-level autoregressive cross-lagged model (with co-rumination measured via observation). Specifically, for the model where co-rumination is measured via self-report, a multi-level (LGM) model, with intervention arm as the exogenous predictor variable, growth rate of mindfulness skills, emotion regulation skills, and problem-solving skills as the mediating variables and growth rate of co-rumination as the outcome variable. Furthermore, for analysis of the model with co-rumination measured via observations (T0 and T4), we will use a multi-level autoregressive crossed-lagged model, with intervention arm as the exogenous predictor variable, (relative change from T0 to T4 in) mindfulness skills, emotion regulation skills, and problem-solving skills as the (correlated) mediating variables, and (relative change from T0 to T4 in) co-rumination as the outcome variable.

Hypothesis 8 “Girls in the intervention group will demonstrate a change in subjects discussed: girls will demonstrate less problem talk about interpersonal problems and shorter periods of interpersonal problem talk immediately after the intervention period and after 1-year follow-up, relative to girls in the control condition” will be tested using Latent Transition Analysis (LTA). Via LTA it can be tested whether girls transition from one class (e.g., a class consisting of girls who engage a lot in interpersonal problem talk; class 1) to another class (e.g., a class consisting of girls who do not engage a lot in interpersonal problem talk; class 2) over time (i.e., between T0 and T4). Via multi-group testing we will investigate whether the probability of changing from class 1 to class 2 is higher for girls in the intervention arm compared to girls in the control arm.

Hypothesis 9 “The hypothesized intervention effects on (the onset) of depression and anxiety symptoms or disorders and depression contagion and anxiety contagion are differently related to changes in interpersonal components of the conversations between girls” will be tested via a joint LTA and DTSA model. First, classes of girls who do and who do not change in their amount and period of interpersonal subjects discussed will be identified via an LTA. Next, it will be investigated whether the resulting classes retrieved from the LTA (i.e., probability of class-membership for the identified transition classes) is a mediator between the intervention effect and the DTSA model of the onset of depression and anxiety symptoms or disorders.

All analyses will be conducted in structural equation modeling program Mplus (v 8.7 or higher; [106]). Model fit will be determined using the comparative fit index (CFI; critical value ≥ 0.95), the root mean square error of approximation (RMSEA; critical value ≤ 0.06), and the standardized root mean square residual (SRMR; critical value < . 08; [107]). When appropriate, standard errors will be adjusted for clustering of dyads within schools using a sandwich estimator [104]. For hypotheses that include mediation analysis (hypothesis 1 and 5), we will use 10,000 bootstrap resamples with replacement and bias-corrected 95% confidence intervals to test these indirect effects [108]. When appropriate, differences in (indirect) pathways between the intervention and the control arm will be estimated using the DIFFtest option in Mplus (when using the weighted least squares means and variance adjusted (WLSMV) estimator) or the Satorra Bentler chi-square difference test [109]; when using the maximum likelihood estimator with robust standard errors (MLR) estimator).

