The hypotheses are:Girls in the intervention group will have a greater reduction in co-rumination about distress and difficult emotions and feelings, (and thereby) internalizing symptoms and negative affect during the intervention period, immediately after the intervention period and after 1-year follow-up, relative to girls in the control condition.Girls in the intervention group will have a later onset of depressive symptoms or a later onset of depressive disorder and less dyadic depression contagion, immediately after the intervention period and after 1-year follow-up, relative to girls in the control condition.Girls in the intervention group will demonstrate less anxiety, problem talk, a later onset of anxiety symptoms or a later onset of anxiety disorder and less dyadic anxiety contagion during the intervention period, immediately after the intervention period and after 1-year follow-up, relative to girls in the control condition.Girls in the intervention group will experience better friendship quality, higher levels of positive affect and higher levels of interpersonal responses to positive affect of the dyad friend, during the intervention period, immediately after the intervention period and after 1-year follow-up, relative to girls in the control condition.The hypothesized intervention effects on co-rumination will be mediated by the development of mindfulness skills, emotion regulation skills, and problem-solving skills during the intervention period, immediately after the intervention period and after 1-year follow-up.The hypothesized intervention effects on co-rumination will be moderated by self-control: girls with more developed self-control skills will demonstrate greater intervention effects immediately after the intervention period and after 1-year follow-up, relative to girls in the control condition.Girls in the intervention group will experience less anhedonic symptoms, will experience greater feelings of mastery, and will show less health care use during the intervention period, immediately after the intervention period and after 1-year follow-up, relative to girls in the control condition.Girls in the intervention group will demonstrate a change in topics discussed: girls will demonstrate less problem talk about interpersonal problems and shorter periods of interpersonal problem talk immediately after the intervention period and after 1-year follow-up, relative to girls in the control condition.

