### Sample size calculation

Multi-level models are used with individuals nested in dyads. With a clinical relevant effect size, that is, a difference of 1 *SD* (i.e., Cohen’s *d* = 1) between the control and intervention group where high-risk girls (*M* + 1 *SD*) score on average similar to non-high-risk girls on co-rumination (*M*) after the intervention, and a small to moderate effect association between co-rumination and internalizing problems (Cohen’s *d* = 0.50; [15]), which will result in a possible reduction of depressive feelings with 0.50 *SD*, and an ICC of depressive feelings within dyads of 0.20, 80 dyads (40 control, 40 intervention) will be required (Optimal Design; [62]). However, we will aim to oversample to a maximum of 160 dyads in order to identify smaller effects (Cohen’s *d* = 0.35) that are potentially relevant for theory development, as well as our hypothesized mediating and moderating factors as described in the “Data analysis plan” section.

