Summed scores will be computed for each girl that are the total number of responses of each type that the adolescent produce. The decision to use summed scores for the analyses (as opposed to proportion scores, i.e., the percent of responses of each type out of the total number of responses) is based on the idea that the total number of experiences that adolescents have in which they hear positive engaged, negative or humorous response statements (in other words, the cumulative experience of hearing these responses) should have a particular critical influence on friendships.

Finally, all the problem-focused thought units will then be assigned one of the topic codes. The topic codes were generated a priori based on the literature reviewed regarding challenges during adolescence. Three topic codes are interpersonal: family, peers (nonromantic), and romantic interests. Three are not interpersonal: academics, athletics and other extra-curricular activities, and jobs and money. Finally, each problem-focused thought unit will be timed. The number of seconds that friend dyads spent on each problem topic will be summed. For each step, 25% of the dyads will be double coded. Interrater reliability will be computed separately for T0 and T4.

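### Hypothesis 8 predicts less and shorter interpersonal problem talk, but the only between-arm test the article describes is a class-transition probability, which measures neither amount nor duration

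*Protocol article*

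**What the plan says.** Among the hypotheses in the protocol article, Hypothesis 8 opens with a change in the topics discussed and then says what change is expected: "girls will demonstrate less problem talk about interpersonal problems and shorter periods of interpersonal problem talk immediately after the intervention period".

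The section on statistical methods for primary and secondary outcomes assigns this hypothesis to Latent Transition Analysis (LTA) between T0 and T4. It gives two classes as an example, the first being "a class consisting of girls who engage a lot in interpersonal problem talk; class 1". The between-arm comparison is: "Via multi-group testing we will investigate whether the probability of changing from class 1 to class 2 is higher for girls in the intervention arm". No other comparison of the arms is described for Hypothesis 8.

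The data come from the Problem Talk Task, which the article places under the primary outcome variables and schedules at T0 and T4. Under Coding process, "all the problem-focused thought units will then be assigned one of the topic codes"; three codes are interpersonal and three are not. Each such unit is also timed, and "The number of seconds that friend dyads spent on each problem topic will be summed".

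Observed co-rumination from the same task and waves is handled differently under Hypothesis 1: "For analysis (b) with co-rumination measured via observations (T0 and T4), we will use a multi-level autoregressive crossed-lagged model". Hypotheses 5 and 6 do the same. The data analysis plan says that it reports only principal features and that the SAP has the detail.

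**The concern.** The hypothesis is about quantities: how much interpersonal problem talk there is and how long it lasts. The comparison named is the probability of leaving one class for another. Three things follow.

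- It gives no estimate of the difference in amount or in seconds, so it cannot say how much less or how much shorter.
- It is informed mainly by girls in class 1 at T0. A reduction that leaves a girl in the same class adds little or nothing.
- One class label merges the two parts of the prediction, so less and shorter cannot be told apart.

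A null transition test could then be reported as no effect on interpersonal problem talk while the recorded seconds and counts showed a reduction. The article gives no reason for treating these measures differently from observed co-rumination.

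**Working it through.** **1. The plan's own sample size.** Inputs from the Sample size calculation section: ICC 0.20 and d = 0.50 with 80 dyads; d = 0.35 with 160 dyads. Two-sided 5% is assumed, as the article does not state it there. The design effect for pairs is 1 + (2 − 1) × 0.20 = 1.2.

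- 80 dyads: 160/1.2 = 133.3 effective girls, 66.7 per arm. 0.50 × √(66.7/2) = 2.887, so power = Φ(2.887 − 1.96) = 0.82.
- 160 dyads: 320/1.2 = 266.7, 133.3 per arm. 0.35 × √(133.3/2) = 2.858, so power = Φ(0.898) = 0.82.

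Both reproduce at about 80% power. Neither concerns observed talk: the section's 0.50 is "which will result in a possible reduction of depressive feelings with 0.50" SD, 0.35 is an unspecified smaller effect, and its target for co-rumination itself is d = 1. Applying 0.35 and 0.50 to interpersonal problem talk is therefore an assumption.

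**2. Dyad level, central case.** This suits the seconds, which are summed per dyad. Assumptions: 80 dyads per arm, normal scores, T0-T4 correlation r = 0.5, d = 0.35, classes known without error, half the dyads in class 1 at T0.

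- T0-adjusted comparison: noncentrality = d/√(1 − r²) × √(160/4) = 0.35/0.866 × 6.325 = 2.556. Power is 0.72 (t, 157 df).
- Transition test: in controls, the chance of being below the border at T4 given above it at T0 is 1/2 − arcsin(0.5)/π = 0.333. With the shift it is 0.481. About 40 dyads per arm contribute. The pooled proportion is 0.407 and the null SE is √(2 × 0.407 × 0.593/40) = 0.110. The SE under the alternative is √((0.222 + 0.250)/40) = 0.109. Power = Φ((0.148 − 1.96 × 0.110)/0.109) = 0.27.

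**3. Dyad level, range.** Simulation over r = 0.3 to 0.7 and class 1 shares of 30%, 50% and 70%; the closed form agrees to within about 0.02.

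| d (assumed) | T0-adjusted comparison | Transition test |
|---|---|---|
| 0.35, r = 0.5 | 0.72 | 0.18-0.32 |
| 0.35, r = 0.3-0.7 | 0.62-0.87 | 0.17-0.36 |
| 0.50, r = 0.5 | 0.95 | 0.32-0.57 |
| 1.00, r = 0.3-0.7 | about 1.00 | 0.72-1.00 |

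**4. Girl level.** This suits the counts. Girls are nested in 160 dyads with dyad-clustered standard errors, over the same r and class shares. The ICC of 0.20 is borrowed from depressive feelings; 0.80 is a sensitivity value.

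| d, ICC | T0-adjusted comparison | Transition test |
|---|---|---|
| 0.35, 0.20 | 0.85-0.98 | 0.30-0.58 |
| 0.35, 0.80 | 0.66-0.91 | 0.24-0.45 |
| 0.50, 0.20 | 0.99-1.00 | 0.49-0.88 |

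Without T0 adjustment, the continuous comparison at d = 0.35 and ICC 0.20 has power of about 0.81. In the null setting checked, the transition test rejected in 6.3% of runs, so its power is if anything slightly flattered.

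**5. The opposite case.** Suppose two real classes lie 2, 3 or 4 SD apart with half the girls in class 1 at T0. The programme acts only by lowering the chance of staying in class 1 from 0.60 to 0.35. The T0-adjusted score then has power 0.37, 0.46 and 0.52. The transition test has 0.42, 0.68 and 0.79 with assigned classes, and 0.83-0.84 if true classes were known. The order reverses.

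**The case against.** The strongest reply is that LTA is not a cut at a percentile. Counts and seconds can enter as full-scale indicators and membership is probabilistic, so a hard split is only a stand-in for the planned model. That stands. A reader might infer that the recorded counts and seconds are thrown away. The article does not support this: it does not name the indicators, and these measures may well be among them. They are coarsened in the between-arm comparison, not unused.

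A reader might also infer that half or more of the power is lost in general. That does not hold. The loss depends on assumed values, is largely gone at d = 1 except when class 1 is small, and reverses in the scenario of step 5. Nor does the article say that the trial is sized to find d = 0.35 to 0.50 on this outcome.

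The opening clause of Hypothesis 8, on change in topics, is a fair target for a latent-class model. The SAP is not shown and may contain a direct comparison, so the point concerns the test as the article describes it. The Discussion lists observed co-rumination, not topic change, among the primary outcomes, and Hypothesis 8 is one of nine. These points limit the weight. None of them turns a transition probability into an estimate of less or shorter talk.

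**Conclusion.** The point holds as a mismatch between the amount-and-duration clause of Hypothesis 8 and the test described for it. It is an analysis choice the article states, not a detail left to the SAP, and it is worth changing.

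The mismatch needs no simulation. The power figures do: they rest on normal scores, hard classes, two-sided 5%, assumed T0-T4 correlations and class shares, and effect sizes borrowed from other outcomes. At d = 0.35 the transition test has roughly 0.17-0.36 against 0.62-0.87 at dyad level, and 0.30-0.58 against 0.85-0.98 at girl level with ICC 0.20. The article presents its classes only as examples and does not claim that the programme works solely by moving girls between separate classes, so the reversed case is possible but not the stated premise.

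A reader might extend the argument to Hypothesis 9, which uses the transition classes as a mediator. No calculation here bears on that joint model, so there is no case for changing it.

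**What to change.** Test the less-and-shorter clause of Hypothesis 8 with T0-adjusted comparisons by arm at T4:

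- **Duration:** total seconds on the three interpersonal topics, analysed per dyad (80 against 80), because seconds are summed per dyad. The within-dyad ICC does not apply here.
- **Amount:** number of interpersonal problem thought units per girl, with girls nested in dyads.

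Use a log or count model if the distributions are skewed, and report each difference with its confidence interval. Keep the LTA as the supporting analysis of change in topic pattern, and leave Hypothesis 9 as planned. If the SAP already contains such comparisons, the article should name them as the test of this clause.

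The cost is wording in the analysis plan; no new data are collected. The downside is that the class-transition result becomes supportive instead of deciding. The change covers T4 only: the task is scheduled at T0 and T4, so neither analysis can address the one-year part of the hypothesis.

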### Trial design

The present study is a parallel group superiority trial design (two cohorts, see Timeline of the interventions and measures) comparing the HFPM intervention arm with a CAU control arm in a two-armed cluster randomized controlled trial. Dyads will be randomly allocated to either the HFPM program or the CAU control condition, with an equal allocation ratio (see also “Randomization, blinding, and treatment allocation”). Blinding for the intervention is not possible.

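### Hypothesis 9 is announced as a joint LTA and survival model but described as two steps with a retrieved class probability as mediator; the two are different estimators and must be reconciled

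*Protocol article*

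**What the plan says.** All statements come from the protocol article, section Statistical methods for primary and secondary outcomes, unless noted.

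- Label for Hypothesis 9: it "will be tested via a joint LTA and DTSA model".
- First step: girls who change and those "who do not change in their amount and period of interpersonal subjects discussed will be identified via an LTA". Arm is not mentioned in this step.
- Second step: it is examined "whether the resulting classes retrieved from the LTA (i.e., probability of class-membership for the identified transition classes) is a mediator" linking arm to onset.
- Neighbouring Hypothesis 8, also an LTA from T0 to T4: "Via multi-group testing we will investigate whether the probability of changing from class 1 to class 2 is higher" in the intervention arm. Whether Hypothesis 9 reuses that LTA is not stated.
- Inference for indirect effects: "For hypotheses that include mediation analysis (hypothesis 1 and 5"), bootstrap intervals are specified. Hypothesis 9 is not listed, although it tests a mediator.
- Detail is deferred (Data analysis plan): "For an elaborate description of the analyses methods used to test the hypotheses, please see the Statistical Analyses Plan (SAP"). That SAP is not at hand.

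**The concern.** The label and the description cannot both be carried out. In a one-step joint model the transition class is a latent variable inside a single likelihood, and no class probability is taken out and passed on. In the described sequence, the probability from the first model becomes the mediator in the second. This is a stated choice of mediator, not a missing detail.

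The difference matters because an estimated class probability is not the class. If the LTA ignores arm, each girl's probability is pulled toward the pooled class share and the arm difference is diluted. If the LTA uses arm, the average is right, but the probabilities vary less than the classes they stand for, so an ordinary standard error is too small. Depending on an unstated choice, the mechanism test is either diluted or falsely precise. How strongly depends on how cleanly the classes separate, not on the programme. The article names uncovering mechanisms of change as part of the trial's objective.

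**Working it through.** The plan gives no figure for Hypothesis 9, so there is none to reproduce. The check asks what the described sequence returns.

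**1. Direction, arm left out of the LTA.** Let *M* be the class (1 = moved from high to low interpersonal problem talk) and *p* its posterior probability. By calibration Cov(*p*, *M*) = Var(*p*), so

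E[*p* | *M* = 1] − E[*p* | *M* = 0] = Var(*p*) / Var(*M*) = R, with R < 1 unless the classes are perfectly separated.

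With two classes, the arm difference in mean *p* is R times the true difference in class share. With four T0-by-T4 patterns the exact factor is the gap in mean *p* between movers and girls who stay high, which is also below 1.

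**2. Size, arm left out.** Large-sample simulation, N = 200,000. From the document: equal allocation. Assumed, because the document gives no values:
- 70% start in the high class, and 10% of the low class move up;
- probability of leaving the high class is 0.30 (control) and 0.50 (intervention);
- log-odds of onset are −0.8 for movers, with a direct arm effect of −0.2;
- the DTSA is a person-period logistic model with five intervals;
- measurement parameters are known and clustering is ignored.

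The true arm-to-class path is *a* = 0.70 × (0.50 − 0.30) = 0.14. The indirect effect is *a* × *b*, where *b* is the class-to-onset log-odds adjusted for arm. Percentages are shares of the value obtained with the true class.

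| Class separation (SD) | Entropy | *a* with posterior | *b* with posterior | *a* × *b* | Share of true *a* × *b* |
|---|---|---|---|---|---|
| 1.5 | 0.44 | 0.036 (26%) | −0.731 (91%) | −0.027 | 23% |
| 2 | 0.58 | 0.060 (43%) | −0.768 (95%) | −0.046 | 41% |
| 2.5 | 0.70 | 0.082 (58%) | −0.772 (97%) | −0.063 | 57% |
| 3 | 0.81 | 0.105 (74%) | −0.785 (97%) | −0.082 | 72% |
| 4 | 0.93 | 0.127 (89%) | −0.783 (99%) | −0.100 | 88% |

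The loss lies almost wholly on the arm-to-class path. Part of it moves to the direct path: at entropy 0.44 the direct effect goes from −0.201 to −0.276.

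**3. Estimate, arm in the LTA.** The same data with arm-specific transition probabilities, as in Hypothesis 8, recover 99–102% of *a*, 93–99% of *b* and 92–100% of *a* × *b*. The shrinkage is essentially gone.

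**4. Uncertainty, arm in the LTA.** Take two classes with known measurement parameters and class share π. The estimated share has variance π(1 − π)/(nR). Treating *p* as observed gives Var(*p*)/n = Rπ(1 − π)/n. The ratio of naive to true variance is R², so the naive standard error is R times the true one, and a nominal 5% two-sided test has size 2[1 − Φ(1.96 R)]. As an approximation, put the recoveries of *a* from step 2 in for R:

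| Separation (SD) | R | 1.96 × R | Approximate size | Simulated, 320 girls |
|---|---|---|---|---|
| 2 | 0.43 | 0.84 | 40% | 39% |
| 2.5 | 0.58 | 1.14 | 26% | 26% |
| 3 | 0.74 | 1.45 | 15% | 19% |
| 4 | 0.89 | 1.74 | 8% | 8% |

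A second set of 2,000 null runs with 320 girls (70% starting high, transition 0.30 in both arms, measurement parameters known, clustering ignored) gave 47%, 28%, 17% and 9%. With arm left out, the error rate was about 5%, but the effect is then diluted as in step 2.

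**5. One-step model.** The class stays latent, so neither problem arises from this source.

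**The case against.** The strongest reply is that the text never calls the mediator observed and never says that arm is left out. It says joint, and the ordering words could describe how the model is built up. The Hypothesis 8 LTA just above is multi-group by arm; if Hypothesis 9 reuses it, the indirect effect is recovered at 92–100%. The article also reports only principal features and refers to an SAP that is not shown. All of this stands against any categorical claim. A reader might infer that the plan certainly shrinks the programme's mediated effect. The document does not support that, because both conditions for it are inferred. A reader might also infer that girls will be assigned to their most likely class, but the text speaks only of a probability.

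The reply does not remove the point. What is retrieved and used as mediator is a principal feature, and as written it contradicts the label. Including arm cures the shrinkage but not the understated uncertainty.

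Two limits on consequence also stand. With 320 girls and transitions of 0.30 against 0.50, power for the arm-to-class path with the arm-free posterior, against an LTA with arm, was 44% against 56%, 59% against 68%, 69% against 75% and 74% against 81% at 2, 2.5, 3 and 4 SD. That is a loss of 6 to 12 percentage points, much less than the shrinkage alone suggests, because imperfect separation costs the better model information too. Hypothesis 9 is also absent from the eight hypotheses listed under Main study aim, research question, and hypotheses.

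**Conclusion.** The point holds in conditional form. What the document itself establishes is the contradiction: a joint model is announced, and a sequence with a retrieved class probability as mediator is described.

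The statistical consequence depends on how the sequence is carried out. With the probability treated as observed and arm left out, the indirect effect is 23% to 88% of the truth for separations from 1.5 to 4 SD, and part of the effect moves to the direct path. With arm included, the estimate is close to right, but the arm-to-class test rejects in about 8% to 39% of null runs at a nominal 5% for separations from 4 down to 2 SD (9% to 47% in the second set). If a one-step model is what is meant, only the wording needs correcting.

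All sizes rest on assumed class shares, transition and onset parameters, known measurement parameters and no clustering. The actual entropy cannot be known from the document. Hypothesis 9 is a mechanism question, so the primary treatment comparisons do not depend on it.

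**What to change.** State one estimator for Hypothesis 9, in the same terms in the article and the SAP:

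- either a one-step LTA and DTSA model in which arm predicts the T0-to-T4 transition and onset hazards are class-specific;
- or a bias-adjusted three-step method (ML or BCH correction) with arm in the model.

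Delete the retrieved class-membership probability as mediator. Say explicitly how arm enters the LTA and whether the Hypothesis 8 LTA is the one used. Add Hypothesis 9 to the mediation hypotheses alongside 1 and 5, with an interval method suited to the chosen model.

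The cost is plan wording and Mplus syntax, longer run time and some convergence checks. No new data are needed.
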